### Trial Design

In this proposed study, we will use a single-blind randomised controlled trial design with two-armed repeated measures. The trial design complies with the Consolidated Standards of Reporting Trials (CONSORT) statement (61). In our two-armed design, we will use TPS as an intervention group and a waitlist control group. At the same timepoints, we will appropriately compare the effect of the TPS treatment between those who received it in the intervention group and those who did not receive it in the waitlist control group (62). Both groups were measured at baseline (T_1_), immediately after the intervention (T_2_), and at the 3-month follow-up (T_3_). A total of 30 community-dwelling subjects, aged 18 and above, will be recruited. All subjects will be computer randomised into either the intervention group or the waitlist control group, balanced by gender and age on a 1:1 ratio. All subjects in each group will have to undertake fMRI before and after six 30-min TPS sessions, which will be completed in 2 weeks' time. Baseline measurements and post-TPS evaluation of the psychological outcomes (i.e., depression, cognition, anhedonia, and IADL) will also be conducted on all participants. Based on the previous studies, a 3-month follow-up is sufficient to assess the long-term sustainability of the TPS intervention (60).

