#### Cognition

Global cognition will be measured using the Hong Kong Chinese version of the Montreal Cognitive Assessment (MoCA) (68). The MoCA is a one-page test with a maximum score of 30. One point is added if the person has 12 years of education or less. A score of 23–26 represents mild cognitive impairment, 17–22 represents moderate impairment, and 16 or below suggests severe impairment and dementia. Working memory, executive function, and attention will be measured by forward and backward digit span, the category verbal fluency test, and the Trail Making Test (TMT) Parts A and B.

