### Statistical Methods

#### Statistical Methods for Primary and Secondary Outcomes

##### Data Analysis Plan

Data will be analysed by the SPSS for Windows, version 27. The normality of the primary outcome (depression) scores will be tested by the Kolmogorov-Smirnov test. If significant differences between sociodemographic variables are found, covariates will be used as a control or confounding variables in the main analysis. For Objective 1, multilevel modelling analysis will be used to investigate changes in the outcome measures (depression) at each time interval (2 weeks and 3 months) with respect to their baseline measurements to examine the effects of TPS. A two-level model will be built, with repeated time points at level 1 and respondents at level 2. The baseline difference between groups will be tested using the Wald test based on the regression coefficient estimates of the indicator. The changes in the outcome measures over time will be included in the fixed part of the model to estimate change from baseline to 2 weeks and from baseline to 3 months. To assess the effects of TPS over time, interaction terms will be included in the fixed part of the model. The significantly different demographics between groups identified in step one of the analysis and other possible confounders will be adjusted by including them in the main-effect model. The within-respondent random effects of the outcome measurements will be taken into account by the level-2 variance in the model. For Objectives 2, 3, and 4, pairwise comparison and other hypotheses on the intervention effects will be tested using a generalised Wald test with an adequate degree of freedom from the modelling analysis (70). The same model, which will be conducted separately for each outcome, will be used to investigate the effect of interventions on secondary outcome measures. To assess the effects of TPS, an intention-to-treat (ITT) analysis will be performed on all participants who undergo random allocation. A multiple imputation method will be used to handle missing data. The pooled results of the multilevel analyses with five multiple imputations will be presented. A sensitivity analysis will be performed by comparing results from analysis datasets with and without missing data imputation. In all tests, significant differences between groups will be detected with a 95% CI, and *p*-values of < 0.05 (two-tailed) will be considered significant. For Objective 5, the neurological rs-fMRI data, longitudinal VBM will be used to examine whether TPS produces local changes in grey matter. Specifically, relative local increases and decreases between pre- and post-intervention scans will be compared within and between study groups. The diffusion MR data will be analysed using the diffusion tensor model. After a mathematical diagonalization process, the eigenvectors and eigenvalues describing the tensor ellipsoid will be determined. Then, two standard diffusion indices will be obtained which are the following: (1) the apparent diffusion coefficient and (2) the fractional anisotropy. DTI scans pre- and post-treatment will permit the assessment of changes in axial diffusivity, with lower values being interpreted as the structural enhancement of white matter. For the cognitive data analysis, general linear modelling (GLM) will be used to compare the difference in performance in the forward and backward digit span, the Stroop test, the category verbal fluency test, and the TMT Parts A and B between the TPS group and the waitlist control group. Performance on the TMT between the TPS group and the waitlist control group will be analysed by one-way repeated-measures ANOVA. Participants' narrative feedback on TPS will be analysed with descriptive content analysis.

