### Limitations of This Study

There are some limitations that need to be addressed in this protocol. First, since we will execute the first pilot RCT nationwide interrogating the effects of TPS on MDD, we can only use existing NIBS studies like TMS and tDCS to act as a comparison for our findings. Since both TMS and tDCS use non-invasive neuromodulation technology by electrical stimulation, the mechanism will be somehow different from TPS which uses ultrashort ultrasound waves in the stimulation of the human brain. Thus, our findings will need to be interpreted with caution. Second, participants in the waitlist control group will be given the identical TPS intervention, albeit in different timepoints, but they will all receive the same TPS pulse/frequency/energy in this TPS trial. Third, the TPS machine itself may have a potential placebo effect which may bias the results. Fourth, there could be a potential risk of contamination if our waitlist control group utilised self-prescribed pharmaceutical input or other TCM modalities (e.g., herbal soup and acupuncture) to treat their symptoms of depression while waiting the TPS treatment. Such contamination may impact the receptivity and efficacy of our TPS intervention. Fifth, participants will be administered the same sets of psychological instruments at three different time points so there is a potential risk that some participants may recall some contents of these instruments. To prevent this, our research personnel will not provide accurate answers to these tests throughout each study phase to minimise recall bias. Last but not least, individuals with severe depression with fleeting suicidal ideas will be excluded in this study, and thus, the efficacy of TPS on these severely depressive and suicidal community-dwelling individuals will remain unknown. Future replication of a multi-centre study may adopt a double-blinded, sham-controlled RCT to philtre out the placebo effects on a larger sample.

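### The Trail Making Test has three overlapping analyses with none named as deciding, and the one described as a comparison of TPS with waitlist is, as named, a test with no arm term

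*Protocol article*

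**What the plan says.** The Cognition section makes the TMT one of several secondary cognitive measures: "Working memory, executive function, and attention will be measured by forward and backward digit span, the category verbal fluency test, and the Trail Making Test", Parts A and B. The Trial Design section sets out two arms: "In our two-armed design, we will use TPS as an intervention group and a waitlist control group". Outcomes are taken at baseline, immediately after the intervention and at three months.

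The Data Analysis Plan then covers the TMT in three places:

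- **Multilevel model.** The two-level model described for depression extends to the secondary outcomes: "The same model, which will be conducted separately for each outcome, will be used to investigate the effect of interventions on secondary outcome measures". It carries the arm comparison over time: "To assess the effects of TPS over time, interaction terms will be included in the fixed part of the model". Objectives 2 to 4, which include cognition, are tied to a Wald test from this modelling.
- **General linear model.** In the cognitive paragraph, "general linear modelling (GLM) will be used to compare the difference in performance in the forward and backward digit span". The same sentence goes on to list "the TMT Parts A and B between the TPS group and the waitlist control group".
- **One-way repeated-measures ANOVA.** The next sentence reads: "Performance on the TMT between the TPS group and the waitlist control group will be analysed by one-way repeated-measures ANOVA".

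No sentence ranks these three. The Limitations section adds that "participants will be administered the same sets of psychological instruments at three different time points", and accepts that some participants may remember test content.

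**The concern.** The ANOVA sentence asks a between-group question and names a within-person test. A one-way repeated-measures ANOVA has one factor, measured repeatedly in the same people, which here is visit. Its F test asks whether TMT performance changes across visits in everyone analysed. If arm were the single factor instead, the analysis would not be a repeated-measures one.

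This matters because both arms repeat the same instruments, and the protocol itself recognises recall as a risk. Improvement from repetition alone would appear as a visit effect in both arms. The cognition objective is worded as improvement after the two-week course, maintained at three months, so a significant visit effect could be mistaken for meeting it. With three analyses and no stated order, a significant visit test could be reported beside a null arm contrast, and nothing in the text says which one counts.

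**Working it through.** The plan gives no power or error figure for the TMT, so there is nothing of its own to reproduce. The check has two parts.

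**1. What each test can see.** Inputs from the document: N = 30, allocation 1:1 (15 per arm), three visits, two-sided 0.05.

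- One-way repeated-measures ANOVA: visit df = 3 − 1 = 2; error df = (30 − 1) × 2 = 58. There is no other tested term.
- Arm-by-visit (mixed) ANOVA: arm df 1, 28; visit df 2, 56; arm-by-visit df 2, 56, with 56 = (30 − 2) × 2.

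Only the second layout contains a term that compares TPS with waitlist.

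**2. What the visit test does when TPS has no effect.** Assumed, not in the document: a retest gain of g SD at both later visits in both arms, a between-visit correlation ρ, compound symmetry and no dropout.

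The visit means are 0, g, g. Their squared deviations from the mean sum to (2/3)g². The noncentrality of the visit F test is

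λ = N × (2/3)g² / (1 − ρ) = 20g² / (1 − ρ).

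For g = 0.3 and ρ = 0.7, λ = 20 × 0.09 / 0.3 = 6.0. A noncentral F with df 2, 58 then exceeds its 5% critical value with probability 0.56. Simulation (20,000 trials per cell) agrees:

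| Retest gain (SD) | ρ = 0.5 | ρ = 0.7 | ρ = 0.8 | Arm-by-visit test, all ρ |
|---|---|---|---|---|
| 0 | 5% | 5% | 5% | 5% |
| 0.2 | 18% | 27% | 39% | 5% |
| 0.3 | 36% | 56% | 75% | 5% |
| 0.5 | 79% | 96% | 99% | 5% |

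The arm-by-visit test stayed between 4.8% and 5.3% throughout.

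**3. The opposite error.** Suppose the waitlist arm moves by +0.25 SD and the TPS arm by −0.25 SD from baseline, with ρ = 0.7. The visit means averaged over arms are flat, so the one-way test has nothing to find. It rejected in 4% of simulated trials. For the arm-by-visit test, λ = 20 × 0.25² / 0.3 = 4.17, which gives 41% by the noncentral F (df 2, 56) and 41% in simulation.

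**The case against.** The strongest reply is that the TMT does not depend on this sentence. The sentence just before it compares the TMT between arms by general linear model. The multilevel model with interaction terms is run for each secondary outcome, and the cognition objective is tied to that model's Wald test. This stands. A reader might infer that the cognition objective would rest on a p-value reflecting practice, or that TPS is never tested against waitlist on the TMT. The document supports neither inference. That objective also covers the MoCA, digit span and verbal fluency, which the ANOVA sentence does not touch.

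A second reply is that the authors probably meant an arm-by-visit ANOVA and misnamed it, since the sentence speaks of the two groups and the section says its tests look for differences between groups. That is plausible. It means the false-positive rates cannot be presented as what the trial will produce, because they need a literal reading, a real retest gain, and a visit effect taken as efficacy. It does not rescue the wording: the test as named is still the wrong one, and the order of the three analyses is still open.

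Third, the sizes rest on assumed gains and correlations. The document gives neither, and its remark on recall concerns the instruments in general, not the TMT. This also stands, which is why a range is shown.

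**Conclusion.** The point holds in a limited form. One of three TMT analyses is stated wrongly for its stated purpose, and the plan does not say which of the three decides. The mismatch follows from the test's name and the two-arm, three-visit design, and needs no assumption. The size of the possible error does need assumptions. If the ANOVA is run as named and its visit effect read as a TPS effect, the false-positive rate is 18% to 99% for assumed gains of 0.2 to 0.5 SD and correlations of 0.5 to 0.8. It is about 5% if there is no retest gain. The test can also miss a true arm difference, as in the 4% against 41% example. The consequence is confined to one secondary cognitive measure. The HAM-D-17 analysis and the other cognitive tests are not affected.

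**What to change.** Delete the one-way repeated-measures ANOVA sentence. State that the group-by-visit terms of the multilevel model already in the Data Analysis Plan are the single deciding analysis for TMT Parts A and B. The terms to report are the arm contrast in change from baseline immediately after the intervention, and the same contrast at three months only as far as the waitlist arm is still untreated then. Remove the TMT from the general linear model sentence, or label that analysis supportive. The other cognitive tests keep their own contrasts for the cognition objective. A log scale for the TMT is optional, since the document does not say how the test is scored or distributed.

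The cost is one sentence deleted and one or two reworded. No new data, visits or participants are needed.

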
### Interim Analyses

Only the PI will have access to all participants' data. Should any participants suffer from any adverse effect during or after the TPS treatment, they will be duly assessed by the PI and TPS treatment will be terminated as deemed necessary.

### Methods for Additional Analyses (E.g., Subgroup Analyses)

Subgroup analyses will be conducted between the TPS group and the waitlist control group in terms of the primary and secondary outcomes.

### Methods in Analysis to Handle Protocol Non-adherence and Any Statistical Methods to Handle Missing Data

Multiple imputations will be used to manage missing data in any treatment phrases.

### Plans to Give Access to the Full Protocol, Participant Level-Data, and Statistical Code

Anonymous data is available on request.

## Oversight and Monitoring

### Composition of the Coordinating Centre and Trial Steering Committee

Since this is a small-scale study comprising 30 subjects, the PI will closely monitor the progress and intervention of this trial. In addition, the PI will organise regular group meetings with the project team members to update the progress of the study until the completion of this trial.

### Composition of the Data Monitoring Committee, Its Role, and Reporting Structure

Data monitoring committee is not required in this trial as there is no competing interest between the sponsor and the project team members. The sponsor is not involved in the research design, data collection, and execution of this study.

### Adverse Event Reporting and Harms

#### The Safety Issue of TPS

Transcranial pulse stimulation uses very low energy for brain stimulation. *In vivo* animal TPS study did not cause any tissue damage despite using 6- to 7-fold higher energy levels compared with those in human studies. Furthermore, the intervention did not cause any serious adverse effects such as intracranial bleeding, oedema or other intracranial pathology, as confirmed with MRI in a previous AD study. Few subjects reported headache (4%), pain or pressure (1%), and mood deterioration (3%) (60). The Clinically Certified (CE) marked TPS system has proven to be safe in more than 1,500 treatments.

#### Adverse Effects and Risk Indicators

A checklist of potential adverse effects associated with TPS administration will be generated from existing literature (30). The checklist will be used to monitor tolerability and adverse events in each session throughout the intervention.

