### Provisions for Post-trial Care

Participants who are finished receiving the TPS treatment will have a follow-up assessment at a 3-month period. They could contact the PI during the post-trial for any potential physical or mental health issues related to the TPS treatment.

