#### Primary Outcomes

##### Depression

Hamilton Depression Rating Scale-17 (65) will be used to measure symptoms of depression and participants' mood and depression severity. HAM-D-17 is a widely used reliable measurement of depressive and mood symptoms. Scores will range from 0 to 52, with higher scores indicating more severe depression. Clinical response will be defined as a reduction of 50% or more in the HAM-D-17 score. A HAM-D-17 score of 7 or less will be used as an indicator of remission.

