### Data Collection and Management

#### Plans for Assessment and Collection of Outcomes

Both groups will be measured at baseline (T_1_), immediately after the intervention (T_2_), and at the 3-month follow-up (T_3_; refer to Figure 5 CONSORT flow diagram). Based on the previous studies, a 3-month follow-up is sufficient to assess the long-term sustainability of the TPS intervention (60). A trained clinician investigator who is not involved in the intervention will perform the assessments. The primary and secondary outcomes will be assessed at baseline, immediately after the intervention, and 12 weeks after the intervention.

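### The only adverse-event checklist described is tied to TPS sessions, so non-mood harms have no structured collection at baseline, in the untreated waitlist window or in the 3-month follow-up

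*Protocol article*

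**What the plan says.** All references are to the Protocol article.

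- **Adverse Effects and Risk Indicators** describes a checklist of TPS-associated effects drawn from the literature, and says when it is used: "The checklist will be used to monitor tolerability and adverse events in each session throughout the intervention".
- **The Safety Issue of TPS** names the harms seen in the earlier Alzheimer's disease study: headache 4%, pain or pressure 1% and mood deterioration 3%.
- **Interim Analyses** gives a reactive route: "Should any participants suffer from any adverse effect during or after the TPS treatment, they will be duly assessed by the PI".
- **Provisions for Post-trial Care** gives a participant-initiated route: "They could contact the PI during the post-trial for any potential physical or mental health issues related to the TPS treatment".
- **Plans for Assessment and Collection of Outcomes** fixes what the common visits collect: "The primary and secondary outcomes will be assessed at baseline, immediately after the intervention, and 12 weeks after the intervention". The outcomes listed are depression, anhedonia, IADL, cognition and neuroimaging. No adverse-event measure is among them.
- **Depression** (primary outcome) says that HAM-D-17 "will be used to measure symptoms of depression and participants' mood and depression severity". On the assessor, the article says: "A trained clinician investigator who is not involved in the intervention will perform the assessments".
- **Intervention Description** gives both groups six sessions over two weeks, the waitlist group at a later time.

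**The concern.** A checklist that exists only where there is a session follows exposure. In the T1–T2 window one randomised group is questioned repeatedly and the other is not questioned. Headache and similar complaints can occur without any stimulation, so the untreated group is needed to show how often they do. As written, the plan gathers no structured information on them from that group while it is untreated, and describes no checklist at baseline that would separate new symptoms from old ones.

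After the last session, an event is recorded only if it comes to the PI's notice or if the participant makes contact. The contact route is worded around problems related to TPS, so it depends on the participant's own view of cause. A delayed or slowly developing symptom could go unrecorded.

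The article describes the trial as the first pilot RCT of TPS in depression and as groundwork for a larger trial, and it has no data monitoring committee. Whatever tolerability profile it reports is likely to be carried forward.

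**Working it through.** The plan gives no figure to reproduce here. The check sets the collection windows side by side and then sizes the consequence.

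**1. What is collected, and when**

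| Window | Checklist, TPS group | Checklist, waitlist group | HAM-D-17 |
|---|---|---|---|
| T1 | none described | none described | both groups |
| T1 to T2 | up to 6 times | 0 | none between visits |
| T2 | none described | none described | both groups |
| Waitlist group's own TPS course | not applicable | up to 6 times | none described |
| Last session to T3 | 0 (reactive or passive only) | 0 (reactive or passive only) | none between visits |
| T3 | none described | none described | both groups |

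The table takes T2 in the waitlist group to fall before its own TPS. That follows Trial Design, which compares treated with not-yet-treated participants at the same timepoints.

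**2. Share of time without a checklist.** The course takes 2 weeks and T3 comes 12 weeks after it: 12 / (2 + 12) = 86%.

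**3. What unequal questioning could produce.** Inputs: 30 participants allocated 1:1, so 15 per group. The 2-week background rate of a symptom such as headache is an assumption, 20% with a range of 10–30%; the documents give none. Assume no TPS effect at all.

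- Expected reports in the TPS group: 15 × 0.20 = 3 (range 15 × 0.10 = 1.5 to 15 × 0.30 = 4.5).
- Structured reports in the waitlist group: 0, because nobody asks.
- Two-sided Fisher exact p for 4/15 v 0/15 is 0.0996. For 5/15 v 0/15 it is 2 × C(15,5) / C(30,5) = 2 × 3003 / 142506 = 0.042.
- Chance of 5 or more reports in 15: 16% at a 20% background rate (1% at 10%, 48% at 30%).

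This shows what would follow if the two counts were set side by side. It is not a forecast of what the trial will report.

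**4. What equal questioning could and could not deliver.** Take the article's rates for the non-mood harms as per participant (an assumption, since their unit is not stated).

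- Chance of at least one event in 15, 1 − (1 − p)^15: headache at 4%, 45.8%; pain or pressure at 1%, 14.0%.
- With no events, the one-sided 95% upper limit is 1 − 0.05^(1/15) = 18.1% for 0/15 and 1 − 0.05^(1/30) = 9.5% for 0/30.
- Fisher power for 4% v 0% with 15 per group is about 0.02%.

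Equal collection removes the asymmetry and gives honest intervals. It does not support a significance test.

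**The case against.** **Mood is already covered.** A reader might infer that mood deterioration goes unmeasured while the waitlist group waits and after treatment. It does not: HAM-D-17 is scheduled in both groups at T1, T2 and T3, with an assessor outside the intervention. This objection stands, and the point is confined to non-mood harms. Worsening that comes and goes between visits could still be missed, and HAM-D-17 is not named as a harm measure.

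**Attribution is limited anyway.** A reader might also conclude that the checklist schedule is what stops the trial attributing harms to TPS. The documents do not support that. There are 30 participants, no sham arm, and TPS for everyone. Participant Timeline allows about a month for all interventions, which suggests (an inference) that the waitlist group is treated soon after T2, leaving no untreated comparator at T3. This stands; the checklist adds to these limits and is not their main cause.

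**No between-group safety comparison is planned.** Neither the Data Analysis Plan nor the section on additional analyses states one, so it cannot be said that the trial will report a false excess. This stands. The asymmetry matters for anyone who later sets the counts side by side, and it prevents a fair descriptive comparison.

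**The article is condensed.** A fuller protocol may hold a visit-level adverse-event schedule, and the text does not say that the checklist is used only in sessions. This lowers confidence but does not remove the point: the dedicated harms section states when the checklist is used, and the visit schedule is stated to cover the primary and secondary outcomes.

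**Other provisions exist.** Medical comorbidity (CIRS) and history are recorded at baseline, participants are retained after discontinuation, and the PI assesses adverse effects during or after TPS. These help. None of them asks both groups the same symptom questions at the same times.

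**Conclusion.** The point holds in a limited form. Followed as written, the plan has no structured collection of non-mood harms at baseline, in the waitlist group before its own TPS, or after the last session in either group. In the only randomised untreated window the questioning is up to six times against none, and about 86% of the period from first session to T3 relies on reactive or participant-initiated reporting. The consequences are an avoidable ascertainment asymmetry and a risk of missing delayed events.

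The conclusion rests on reading the stated session schedule as complete and on T2 in the waitlist group preceding its TPS. The 20% (10–30%) background rate is illustrative, and the conclusion does not depend on it. The documents do not support saying that mood worsening is missed, that the checklist alone prevents attribution, or that the eventual safety conclusion will be wrong. This is a worthwhile, inexpensive improvement, not a defect that undermines the trial.

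**What to change.** 1. Give the same checklist, with one open question, to both groups at T1, at T2 (the waitlist group before its first TPS session) and at T3, in addition to each session.
2. Record every event, whether or not the participant or staff think it related to TPS.
3. Report HAM-D-17 worsening from baseline as a harm alongside the checklist.
4. Present T1–T2 incidence by randomised group, and session-level and T3 events, descriptively with exact intervals and without a significance claim.

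As Trial Status gives recruitment as completed, any visit already past cannot be recovered. In that case the report should state which windows had structured collection and should not set session counts against an unquestioned waitlist group.

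Both groups already attend these visits, so no new visit is needed. The cost is slightly longer visits and more events to record. No change to treatment is involved.
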